## 10.0 OFF TREATMENT/OFF STUDY CRITERIA

Each subject has the right to withdraw from the study at any time without prejudice. The investigator may discontinue any subject's participation for any reason, including adverse event or failure to comply with the protocol (as judged by the investigator such as compliance below 80%, failure to maintain appointments, etc.).

Should a subject withdraw from the study, the reason(s) must be stated on the case report form, and a final evaluation of the subject should be performed. (See Section 9.2)

### OFF TREATMENT CRITERIA

1. Progression of Disease: Remove patient from protocol therapy at the time progressive disease is documented.  
Disease progression is defined as: Progressive neurologic abnormalities not explained by causes unrelated to tumor progression (e.g. anticonvulsant or corticosteroid toxicity, electrolyte abnormalities, hyperglycemia, etc.) or a greater than 25% increase in the measurement of the tumor by MRI/CT scan. If neurologic status deteriorates, on a stable or increasing dose of steroids, or if new lesions appear on serial MRI/CT, further study treatment will be discontinued.
2. Extraordinary Medical Circumstance: If at any time the treating physician feels constraints of this protocol are detrimental to the patient's health, remove the patient from protocol therapy.
3. Patient's refusal to continue treatment: In this event, document the reason(s) for withdrawal.
4. Failure to comply with protocol (as judged by the investigator such as compliance below 80%, failure to maintain appointments, etc.).
5. Patients who experience unacceptable toxicity, including patients who would require a 2nd dose reduction.
6. Delay in treatment > 14 days.

### OFF STUDY CRITERIA

- 1) Patients will only be off study at time of death. (All patients will be followed every 2 months for survival.)

## 11.0 STATISTICAL CONSIDERATIONS

### **11.1 Overall Objective**

The overall objective of this study is to assess the safety and efficacy of the R-(-)-gossypol (AT-101) in treating adult patients with recurrent glioblastoma multiforme (GBM). The mechanism of the AT-101 is to inhibit the heterodimerization of Bcl-2, Bcl-xL, Bcl-W, and Mcl-1 with pro-apoptotic members of the Bcl-2 family at submicromolar affinity (Investigator's Brochure, 2006). The overall survival is considered the most informative measurement to estimate the clinical benefit regarding to this treatment. Currently, there is rarely any effective treatment existing for this group of patients.

### **11.2 Primary Objective**

To estimate an overall survival, the primary objective of the study is to estimate the overall failure rate compared to the failure rate of the NABTT historical phase II clinical trial database in the same patient population. There are 62 GBM patients who participated in three closed NABTT phase II clinical trials and were treated with single or combination of experimental chemotherapies (protocol number: 9502, 9506, 9706, 9711, and 2111). The estimated historical hazard rate is 1.67 per person-year of follow-up (95% CI: 1.3, 2.14) and an estimated historical median time of survival is 5 months.

The primary endpoint is death. The survival time is defined from time of first day of the treatment to death occurrence. The overall failure rate is expressed as hazard of failure per person-year of follow-up (the number of deaths divided by the total exposure time in the study cohort). The total patient population of this study is defined as all patients who have met eligibility criteria, not met ineligibility criteria and signed informed consent, which will be included in the statistical estimations.

To estimate the overall failure rate with sufficient precision, a total of 52 events are required from 56 patients at an accrual rate of 4 patients per month for 14 months, and with 1.5 years of additional follow-up (total study duration is 2.7 years). We assume that patients in the study will have an overall failure rate of 1.25 per person-year of follow-up, about 25% reduction compared to a hazard rate of 1.67 shown in the relevant NABTT historical database. The 52 events among the 56 patients during the planned follow-up will yield 80% power to detect an observed hazard ratio of 0.75 (1.25 vs. 1.67) to be statistically significant at an alpha level of 0.1 (one-side, A Methodologic Perspective, Piantadosi 1997). The 25% reduction in hazard rate translates into a 33% increase in median time of survival (from 5 month to 6.65 month). Moreover, the total of 52 events will yield 90% power to detect a 30% reduction in observed hazard ratio of 0.7 (1.17 vs 1.67) to be statistically significant, which increases the median time of survival in 40% (from 5 month to 7 month).

The overall failure rate will be estimated along with 95% confidence intervals. A median time of survival will be estimated using standard methods.

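### Section 11.2 sets alpha and power as if the historical rate of 1.67 were exact; with its sampling error counted, the comparison has about 17% error with 72% power, or 10% error with 60% power

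*Protocol*

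**What the plan says.** Section 11.2 makes the primary objective an estimate of the overall failure rate (deaths divided by total exposure time), set against the rate in a database of earlier phase II trials. On the source it says: "There are 62 GBM patients who participated in three closed NABTT phase II clinical trials". On the rate: "The estimated historical hazard rate is 1.67 per person-year of follow-up (95% CI: 1.3, 2.14").

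The sample size follows: "a total of 52 events are required from 56 patients at an accrual rate of 4 patients per month for 14 months". The assumed benefit is: "We assume that patients in the study will have an overall failure rate of 1.25 per person-year of follow-up", described as "about 25% reduction compared to a hazard rate of 1.67 shown in the relevant NABTT historical database". The power claim is that the 52 deaths "will yield 80% power to detect an observed hazard ratio of 0.75 (1.25 vs. 1.67"), judged by a one-sided test at level 0.1. A second claim gives 90% power at a hazard ratio of 0.70.

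No term for the uncertainty of 1.67 appears in the power statement. Section 11.5 adds a separate rule for moving to a comparative trial: median survival longer by 30%, or a failure rate lower by 26%, than the historical data. It calls such rules partly subjective and dependent on toxicity.

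**The concern.** The protocol gives the historical rate as an estimate with a wide interval, then calculates alpha and power as though the rate were known. If the database rate is too high by chance, an inactive drug looks better than history. If it is too low, an active drug looks no better. Neither risk is counted in the stated 10% error or in the stated 80% and 90% power.

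The stake is how far a reader may trust a significant result from the primary comparison. As stated, alpha and power describe a comparison with the number 1.67. The comparison the section names is with the failure rate of a patient population, and 1.67 only estimates that rate.

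**Working it through.** **Inputs, all from section 11.2:** historical rate 1.67, 95% CI 1.3 to 2.14, 62 patients; new trial 52 deaths; hazard ratios 0.75 and 0.70; one-sided alpha 0.1 (z = 1.2816).

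**1. Reproduce the stated power with 1.67 fixed.** Power = Φ(√52 × |ln HR| − 1.2816).
- HR 0.75: Φ(7.211 × 0.2877 − 1.2816) = 78.6% (79.0% with 1.25/1.67; 79.1% by the exact chi-square version). Stated: 80%.
- HR 0.70: Φ(7.211 × 0.3567 − 1.2816) = 90.2%. Stated: 90%.
- A two-sided 0.1 test gives 66.6% at HR 0.75 and does not fit.

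So the plan's figures are those of a one-sided test against a fixed constant. The implied cut-off is an observed ratio below exp(−1.2816/√52) = 0.837, a rate of about 1.67 × 0.837 = 1.40.

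**2. Uncertainty of the historical rate.** SE of the log rate = ln(2.14/1.3)/3.92 = 0.127. That equals 1/0.127² ≈ 62 deaths, matching the 62 patients. The new trial has SE 1/√52 = 0.139.

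**3. Combine both.** SE of the log ratio = √(1/52 + 1/62) = 0.188. The historical share of the variance is (1/62)/(1/52 + 1/62) = 46%, and all of it is left out of the stated power.

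**4. Operating characteristics with both variances**

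| | One-sided error | Power, HR 0.75 | Power, HR 0.70 |
|---|---|---|---|
| As stated | 10% | 80% | 90% |
| Implied cut-off 0.837 kept | 17.2% | 72.1% | 82.9% |
| Cut-off moved to 0.786 | 10% | 59.8% | 73.1% |

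Formulas:
- Row 2: error = 1 − Φ(0.1777/0.188), power = Φ((|ln HR| − 0.1777)/0.188), where 0.1777 = 1.2816/√52.
- Row 3: cut-off = exp(−1.2816 × 0.188) = 0.786, power = Φ(|ln HR|/0.188 − 1.2816).

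A simulation of 400,000 pairs of cohorts gave 17.1%, 71.8% and 82.7% for row 2, and 9.9%, 59.6% and 72.9% for row 3.

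**5. Dependence on the true historical rate, with the implied cut-off.** If the true rate were 1.30, a drug without effect would pass about 70% of the time. If it were 2.14, a drug with a true ratio of 0.75 would pass about 16% of the time.

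**6. The rule in section 11.5.** A 26% reduction means an observed ratio of at most 0.74, a rate of about 1.67 × 0.74 = 1.24.
- False-positive probability: Φ(ln 0.74/0.188) = 5.5%. With 1.67 exact it is Φ(ln 0.74 × √52) = 1.5%.
- Chance of being met at a true ratio of 0.75: about 47%.

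**7. Sensitivity.** With 55 historical deaths instead of 62, the error at the implied cut-off is 17.9% with 71.5% power at HR 0.75. At a true 10% error, power is 58.2%.

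**The case against.** **Fixed benchmarks are a common convention in single-arm phase II trials, and the stated power is right for one.** This is true: against 1.67 as a constant, the arithmetic is correct. But section 11.2 does not present 1.67 as a target chosen on clinical grounds. It presents an estimate from named trials, prints its interval, and makes comparison with that database the primary objective. The conditional nature of alpha and power is never stated.

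**The objective is estimation.** Sections 1.0 and 11.2 do use that language, and no test procedure is set out. The omission is therefore read from the power arithmetic. That arithmetic is still in the protocol, with claims of significance, an alpha and a power, so it has to be right there whatever a separate analysis plan says.

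**The harm does not reach the decision.** Most of this stands. A reader might infer that an observed rate of 1.40, inside the historical interval, would launch a comparative trial. It would not. It is a 16% reduction (1 − 1.40/1.67), or a median about 19% longer under exponential survival (1.67/1.40), and fails both forms of the section 11.5 rule. Even with the historical variance included, the failure-rate form has about 5.5% false-positive probability, below the nominal 10%. It is nevertheless more than three times the 1.5% that a fixed 1.67 would give.

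**The 17% is an average.** This also stands. It averages over repeats of the historical cohort. The error of this trial depends on the unknown true historical rate and cannot be stated.

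**Conclusion.** The point holds. The stated 10% error with 80% and 90% power applies only to a comparison with an exactly known 1.67. For a comparison with the historical population, there are two consistent descriptions:
- implied cut-off kept: about 17% average error, with power of about 72% at HR 0.75 and 83% at HR 0.70;
- error held at 10%: power of about 60% and 73%.

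A reader might join the worse half of each and conclude that the test has 17% error and 60% power. No single cut-off has both.

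The figures assume exponential survival. The plan's own numbers imply this: ln 2/1.67 × 12 = 4.98 months, against the stated median of 5. They also assume about 62 historical deaths, inferred from the interval because the protocol gives patients and not deaths. They cover sampling error only, with no allowance for differences between the historical cohorts and this one.

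**What to change.** **Preferred.** In section 11.2, define the primary comparison as the ratio of the failure rate in this trial to that of the 62 historical patients, with both variances (SE of the log ratio about 0.188) in the confidence interval and the test. Restate power at one-sided 0.10 as about 60% at HR 0.75 and 73% at HR 0.70. State the number of historical deaths and the person-time, so that the calculation no longer rests on an inference from the interval.

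**Alternative.** Declare 1.67 a fixed benchmark, say that alpha and power are conditional on it, and disclose that the error against the true historical rate averages about 17%. It should not be printed as the error of this particular trial.

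**Cost.** Either change needs only wording and analysis work, with no change in sample size. The price is a less favourable stated power. Restoring 80% power at HR 0.75 with a true 10% error is not realistic: with 62 historical deaths, the new trial would need 1/[(0.2877/2.123)² − 1/62] ≈ 448 deaths, where 2.123 is the sum of the normal quantiles for 10% one-sided error and 80% power.

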### **11.3 Secondary Objectives**

1. To assess the acute and late toxicities associated with the treatment. The proportion of patients with serious or life threatening toxicities will be estimated along with 95% confidence intervals. The frequency of different type toxicities will be tabulated by each cycle of the treatment.
2. To estimate tumor response rate. The probability of tumor response (definition: section 8.1) will be estimated using binomial distribution along with 95% CI.
3. To estimate a 6-month progression-free survival rate. The 6-month progression-free survival is defined as patient who is alive and disease progression free at the time of 26-week (6 months) from first day of the treatment (definition of disease progression: section 10.0). The probability of 6-month progression-free survival will be estimated using binomial distribution.
4. Correlative study: Apoptosis can be triggered through either the intrinsic (mitochondrial) or extrinsic (receptor) pathways. The study will focus on regulators of both the intrinsic (Bcl-2, Bcl-XL, Mcl-1, Bax, Bak) and extrinsic (FLIP, survivin, XIAP) pathways. Serum will be collected for analysis of apoptotic protein levels immediately before the first dose and after one week of therapy. Every effort will be made to collect tumor tissue before and after treatment. Descriptive statistics will be used to summarize the protein expressions and patient's MGMT methylation status.

The Cox's proportional hazard model will be used to explore the association between change of the proteins and patient's survival status.

### **11.4 Interim Monitoring**

This is a single arm, open label, single agent, and fixed dose phase II clinical trial. One planned safety assessment will be performed after the first 25 patients are accrued into the study and have had at least one cycle of the treatment. If the following pertain, the study will be suspended pending review by the ABTC DSMC: lower 95% confidence bound on the rate of toxicities grade  $\geq 3$  (this translates to dose limiting toxicity events of any type) exceeds 18%/ or if 4 or less patients ( $\leq 16\%$ ) achieved disease progression-free survival at 6 months.

Progression-free survival at 6 months has not been proven as a validated survival surrogate. The study uses PFS-6m to describe the nature process of the disease without any effective treatment, which the PFS-6m is about 15% in this patient population. A consensus decision by ABTC, CTEP, and the sponsor is required for stopping the trial earlier, if it is necessary due to any reasons.

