In the initial Phase 1 trial, DLTs were reversible grade 4 elevated ALT/AST at daily doses >40 mg/day (Saleh *et al.*, 2005). The principal AEs seen with daily dosing include grade 1 nausea, diarrhea, and fatigue, but one of six patients receiving 40 mg AT-101 daily experienced grade 4 hypokalemia and grade 3 nausea. Stable measurable disease and a reduction in circulating lymphocytes from about 33,000/dL to 22,000/dL were reported in one patient with CLL after 5 cycles at 10 mg AT-101 daily. Of interest, this patient's lymphocyte count consistently rose during the week off therapy, then decreased once AT-101 was restarted. Other evidence of efficacy has been provided by three patients with non-small cell lung cancer (NSCLC) who remained on study with stable disease (SD) for more than 72 to 123 days; in addition, SD (66+ days) has been reported in a patient with a parotid tumor treated at 40 mg daily AT-101.

Additional Clinical Studies with AT-101

AT-101 is being investigated in several Phase 1-2a clinical trials as a single agent or in combination with standard agents for the treatment of patients with advanced solid tumors, lymphoma, or chronic lymphocytic leukemia. As of November, 2006, approximately 155 patients have been enrolled on 8 Phase 1/2 trials. Most patients have received AT-101 once or twice daily, every day for 21 out of every 28 days, in these trials. Total daily AT-101 doses for these patients have been 5-60 mg. The majority of patients have been treated with AT-101 on a daily schedule; however, alternative schedules are currently being tested.

Clinical trials conducted with AT-101 are ongoing; however, preliminary safety data show that the most common AEs, when AT-101 is administered on a once daily schedule, have been gastrointestinal (GI) and grade 1/2 fatigue. The GI AEs include nausea, vomiting, abdominal pain, abdominal discomfort, diarrhea, constipation, and small bowel obstruction (SBO). The most common SAEs reported include nausea, vomiting, SBO, and ileus, especially after several months of continuous dosing. While some of these SAE reports have been unrelated to AT-101 administration and attributed to disease progression, the majority have been related to AT-101 and have resulted in the hospitalization of research subjects. Reversible elevation of ALT and AST were dose-limiting at doses greater than 40 mg/day, administered daily for 21/28 days, in the initial Phase 1 trial.

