Following periodic safety reviews, Ascenta has modified the dosing schedule of single-agent AT-101 to include a drug 'holiday' and has reduced the dose of single-agent AT-101, when administered daily, to 20 mg/day for 21/28 days. Additionally, Ascenta is also investigating shorter periods of exposure (pulse dosing) of AT-101 as a single agent and in combination with standard agents. The results of these changes were only recently made and the effect of these new doses and schedules on gastrointestinal AEs and SAEs has not yet been fully determined.

As of November 2006, there have been 32 SAEs reported after treatment with oral AT-101. Twenty-four patients have had events that represent, or may represent, small bowel obstruction/ileus. Several of these events were considered by the investigator to be unrelated to AT-101, but nonetheless prompted brief hospitalization and interruption of AT-101 dosing, with resolution of symptoms 2-10 days later. Two patients were successfully re-challenged at a lower dose. These events tended to occur at higher doses and typically had an onset later than 4 weeks after the first dose of AT-101. The dosing regimens associated with these events involved continuous daily dosing or dosing for 21 out of 28 days. It is not clear how recent modifications in the dose and schedule will affect the incidence and severity of these or similar events. Further investigations into other doses and schedules of AT-101 are underway.

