## 4.0 TREATMENT PLAN

### 4.1 Treatment Schema

[figure not shown]

Treatment for this protocol will be administered on an outpatient basis. Each patient will receive 20mg of AT-101 orally every day for 3 weeks (21 days) of each cycle. Each treatment cycle is 28 days. Tumor tissue and blood samples will be obtained from each patient prior to beginning treatment with AT-101 (See section 9.5). Treatment of an individual patient will continue until there is objective or clinical evidence of either disease progression or treatment-related, dose-limiting toxicity, or if the patient decides to discontinue treatment for any reason. All patients will be given drug to take home and a drug calendar that explicitly details how many tablets of AT-101 the patient will be taking each day. The patient will be asked to record the amount of AT-101 actually taken as well as the date and time of each dose in a pill diary.

Prior to starting each treatment cycle the patient must meet the following criteria on Day 1 of each treatment cycle:

- $ANC \geq 1,500/\text{mcL}$
- $\text{Platelets} \geq 100,000/\text{mcL}$
- Non-hematologic toxicity recovered to  $\leq$  grade 1, tolerable grade 2 or pretherapy baseline
- No medical condition or other circumstance (including progressive disease) exists that, in the opinion of the investigator, would make the patient unsuitable for further participation in the study.

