## **9.2 Adverse Event Definition and Reporting**

Patients will be evaluated for toxicity if they have received at least one dose of AT-101.

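### The only study-level numeric toxicity criterion is applied once, before most of the late treatment exposure, and its one-cycle wording leaves the denominator unclear against section 9.2

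*Protocol*

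**What the plan says.** Protocol section 11.4 plans a single look: "One planned safety assessment will be performed after the first 25 patients are accrued into the study and have had at least one cycle of" treatment. Suspension pending review by the data and safety monitoring committee (DSMC) follows if the "lower 95% confidence bound on the rate of toxicities grade" 3 or higher "exceeds 18%/ or if 4 or less patients" reach 6 months without progression. The section gives neither the method nor the sidedness of the bound. On early closure it adds: "A consensus decision by ABTC, CTEP, and the sponsor is required for stopping the trial earlier", without a threshold.

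Three other places bear on this:

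- Section 9.2 defines who is evaluable: "Patients will be evaluated for toxicity if they have received at least one dose of AT-101".
- Section 4.1 sets the cycle length: "Each treatment cycle is 28 days".
- Section 2.0, on clinical experience with AT-101, says of small bowel obstruction and ileus: "These events tended to occur at higher doses and typically had an onset later than 4 weeks after the first dose of AT-101". It also says the most common serious events, which include these two, arose "especially after several months of continuous dosing". It adds that the effect of the sponsor's later dose and schedule changes was not yet clear.

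**The concern.** A criterion for excessive toxicity is useful only if it is applied while the relevant toxicity can still appear and if its denominator is fixed. Here it is applied once. The last of the 25 patients need only have completed 28 days, which is about where the protocol says its main named serious risk typically starts. If the cumulative grade 3 or higher rate became excessive later, no stated criterion would detect it.

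The one-cycle condition also sits awkwardly with section 9.2. A patient taken off treatment for toxicity in week 2 does not complete a cycle, and section 11.4 does not say whether that patient counts. Any omission of this kind lowers the observed rate.

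**Working it through.** **The plan's own figure.** 4/25 = 16%, as section 11.4 states.

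**Timing of the look.** Accrual is 4 per month (sections 3.1 and 11.2) and a cycle is 28 days, or 28/30.44 = 0.92 months. The 25th patient enters at 25/4 = 6.25 months, so the look falls at 6.25 + 0.92 = 7.2 months. Patients outside it: 56 − 25 = 31 (55%).

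**Exposure after the look.** The protocol gives no distribution for time on treatment. I assume it is exponential with hazard h = −ln(S)/6 per month, where S is the proportion progression-free at 6 months. Section 11.4 gives S of about 15%; 25% and 35% are my range. Patient i enters at i/4 months. Expected exposure beyond week 4 is exp(−0.92h)/h per patient in total. By the look it is [exp(−0.92h) − exp(−h(7.17 − i/4))]/h for each patient followed longer than 0.92 months.

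- S = 15%: h = 0.316; 24% seen, 76% still to come.
- S = 25%: h = 0.231; 20% seen, 80% still to come.
- S = 35%: h = 0.175; 17% seen, 83% still to come.

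The 6-month progression-free condition cannot be evaluated one cycle after the 25th entry. If the whole assessment waited until all 25 reached 6 months (6.25 + 6 = month 12.25), the first 25 would supply 41%, 37% or 33% of all exposure beyond week 4. That leaves 59–67% outside the criterion.

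**Where the boundary lies.** Exact (Clopper–Pearson) lower bounds, with α = 0.025 for a two-sided interval and 0.05 for a one-sided bound:

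- Two-sided: 9/25 gives 17.97% (continue) and 10/25 gives 21.1% (suspend).
- One-sided: 8/25 gives 17.0% (continue) and 9/25 gives 20.2% (suspend).

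With a true rate of 30% (assumed), the single look suspends with probability P(X ≥ 10) = 0.19 two-sided, or P(X ≥ 9) = 0.32 one-sided. A final 17/56 (30%) has a two-sided lower bound of 18.8%, above the limit, but nothing in section 11.4 would act on it.

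**Effect of the denominator.** Suppose patients with grade 3 or higher toxicity who stopped in cycle 1 were left out. The numbers stopped are illustrative; the protocol gives no early-stop rate.

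- Two-sided: 10/25 = 21.1% (suspend). One omitted: 9/24 = 18.8% (suspend). Two omitted: 8/23 = 16.4% (continue).
- One-sided: 9/25 = 20.2% (suspend). One omitted: 8/24 = 17.8% (continue). But 10/25 with two omitted gives 8/23 = 18.6%, which still suspends.

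**Repeating the criterion.** For illustration, I apply the same bound without adjustment at n = 25, 31, 37, 43, 49 and 56, with each patient's toxicity status taken as known when counted.

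- True rate 30%: the probability of suspension rises from 0.19 to 0.62 (two-sided) or from 0.32 to 0.73 (one-sided).
- True rate 18%: it rises from 0.8% to 4.2% (two-sided) or from 2.5% to 7.8% (one-sided).

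**The case against.** A reader might infer that section 11.4 drops patients stopped by toxicity in cycle 1. The text does not say so. The one-cycle phrase is most naturally a statement of when the look takes place, and section 9.2 says who is evaluable, so the two can be read together. What stands is an ambiguity.

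A reader might also infer that no safety rule operates after the look. That is wrong. Sections 5.1 and 5.1.1 provide holds, dose modification and bowel work-up. Section 9.4 requires expedited reporting, section 5.4 sends cumulative data to CTEP quarterly, and section 11.4 allows a consensus stop for any reason. These controls act patient by patient or carry no threshold, so only a repeated test of the cumulative rate is missing.

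Nor is the look confined to first-cycle data. At month 7.2 the first 25 patients have a median potential follow-up of 3.9 months, and 20 of them have more than 2 months. Under the exposure model, 55% of their own exposure beyond week 4 has been seen at S = 15%, and 38% at S = 35%. The shares in the working already credit this.

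The earlier bowel events do not give an expected rate for this trial. Section 2.0 counts 24 patients with definite or possible events, with about 155 enrolled. It says that several events were judged unrelated and that events tended to occur at higher doses. Because it also calls the effect of the changed dosing unclear, continued monitoring remains reasonable.

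Finally, a single formal look in a 56-patient single-arm trial is a defensible design choice. That bears on how serious the point is, not on whether the coverage gap exists.

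**Conclusion.** The point holds in limited form. The one study-level numeric toxicity criterion is applied once. At planned accrual, 31 of 56 patients and about 76–83% of exposure beyond week 4 fall outside it; waiting for 6-month data on the first 25 still leaves 59–67% outside. These shares depend on the assumed exponential time on treatment, but the direction is the same across the range tried.

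The denominator is ambiguous rather than wrong. Only if the one-cycle phrase is an evaluability condition would early toxicity stops be lost. Whether that reverses a decision depends on the sidedness of the bound, which is not stated, and on how many patients are lost. This is a cheap improvement, not something that must be fixed before the plan can be used.

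**What to change.** In section 11.4:

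- State that the toxicity criterion counts all patients with at least one dose, as in section 9.2, including those who stopped during cycle 1.
- Keep the first look after the 25th patient's first cycle, timed by calendar so that an early stop does not delay it, and count grade 3 or higher toxicities from all cycles to date.
- Recompute the same criterion (lower bound above 18%) on cumulative data at each later quarterly submission under section 5.4 until the last patient is off treatment, with suspension pending DSMC review if it is crossed.
- Name the interval method and say whether the bound is one- or two-sided.

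The cost is a few sentences and a short quarterly tabulation of data already submitted. Unadjusted repetition raises false suspension at a true 18% rate from about 1–2.5% to about 4–8% in the six-look illustration, and a false alarm leads only to DSMC review. No dose or patient-level rule changes.

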### **3.0 PATIENT ELIGIBILITY CRITERIA**

#### **3.1 Patient Sample**

Sample Size:

56 patients

Accrual Rate:

Approximately 4 patients per month

Gender:

Male and Female

Age:

Patients must be at least 18 years of age.

Race:

Minorities will be actively recruited. No exclusion to this study will be based on race.

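### The single interim look in section 11.4 is timed about five months too early for its own 26-week progression-free criterion, so at planned accrual that criterion is met almost automatically

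*Protocol*

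**What the plan says.** Section 11.4 (Interim Monitoring) plans one assessment: "One planned safety assessment will be performed after the first 25 patients are accrued into the study and have had at least one cycle". At that assessment "the study will be suspended pending review by the ABTC DSMC" if either of two conditions holds. The first is a toxicity bound. The second is worded "or if 4 or less patients", with 16% or less in brackets, and the outcome to be counted is that they "achieved disease progression-free survival at 6 months".

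Section 11.3 defines the endpoint as being "alive and disease progression free at the time of 26-week (6 months) from first day of the treatment". Section 4.1 sets the cycle length: "Each treatment cycle is 28 days". Section 3.1 gives accrual as "Approximately 4 patients per month", and section 11.2 plans "at an accrual rate of 4 patients per month for 14 months".

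Section 11.4 gives no separate, later date for the progression-free criterion. It does not say how to count a patient who is still progression-free but has been followed for less than 26 weeks.

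**The concern.** The look may take place once the 25th patient has completed 28 days, but one of its criteria needs 182 days on the same 25 patients. Few of them can have reached the endpoint by then. A rule triggered by a low count of successes will therefore tend to trigger because of the calendar and not because of the drug.

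Two things are at stake. Applied at the earliest permitted date, the rule would halt enrolment at about half accrual and give the monitoring committee a signal with almost no information on activity. Applied only when all 25 patients are mature, it comes when most of the trial has been enrolled, and because there is only one look it takes the toxicity check with it.

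**Working it through.** **Inputs.** Accrual of 4 per month and 56 patients (sections 3.1 and 11.2); look at 25 patients plus one 28-day cycle (sections 11.4 and 4.1); endpoint at 26 weeks = 182 days (section 11.3); cut of 4 patients; background six-month rate of about 15% (section 11.4). One month is taken as 30.44 days, so 28 days = 0.92 months and 182 days = 5.98 months.

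**The plan's own figures.** 4/25 = 16%, so the printed percentage presupposes 25 patients with known status. 56/4 = 14 months of accrual, as stated. The power figures also reproduce with a one-sample test against a fixed historical rate, Φ(√52 × |ln HR| − 1.282): 0.79 at a hazard ratio of 0.75 (stated 80%) and 0.90 at 0.70 (stated 90%).

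**How many patients are mature at the earliest look (even entry).**
- First patient at month 0: the 25th enters at 24/4 = 6.00 and the look is at 6.00 + 0.92 = 6.92. Patients entered by 6.92 − 5.98 = 0.94 are mature: those at 0, 0.25, 0.50 and 0.75, which is 4.
- First patient at month 0.25: the 25th enters at 6.25 and the look is at 7.17. Patients entered by 7.17 − 5.98 = 1.19 are mature: those at 0.25, 0.50, 0.75 and 1.00, again 4.

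With 4 mature patients, five successes cannot occur. If patients short of 26 weeks do not count as successes, the criterion is met with probability 1. It would be met even if all 4 mature patients were progression-free.

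**Uneven entry.** With Poisson accrual at a mean of 4 per month, the average number mature is 4.3, and about 45% of simulated trials have 5 or more. The probability that the criterion is met is:

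| True six-month rate | 15% | 20% | 24% | 30% | 50% |
|---|---|---|---|---|---|
| P(4 or fewer) | 0.997 | 0.992 | 0.98 | 0.97 | 0.85 |

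**Other accrual rates (even entry).** At 3 per month, 9 patients are mature and the probability is 0.994 at 15% and 0.901 at 30%. At 2 per month, 14 are mature and it is 0.953 and 0.584. At 5 per month or faster none is mature and it is 1.

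**Waiting for all 25.** 6.25 + 5.98 = month 12.23, and 4 × 12.23 = 48.9, so 48 to 49 of 56 are enrolled. Against month 7.17 that is a delay of about 5 months for both criteria. The exact binomial probability of 4 or fewer among 25 mature patients is then:

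| True six-month rate | 15% | 20% | 24% | 30% |
|---|---|---|---|---|
| P(4 or fewer of 25) | 0.68 | 0.42 | 0.24 | 0.09 |

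Only the 15% comes from the Protocol; the other rates are assumptions. The 24% is 0.15^0.75 = 0.241, which supposes that the progression hazard falls by the same 25% that section 11.2 assumes for death.

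**Same cut, reached sooner.** Four or fewer successes in 25 is the same event as 21 or more failures in 25, and it is known as soon as the 21st failure is recorded. In a simulation with even entry, exponential progression-free times and a true rate of 15%, the 21st failure occurs in 68% of trials. Among those, its median time is about month 8.9 if progression is known at once (about 36 enrolled), and about month 9.8 if it is found only at the scans before odd cycles, every 56 days (about 40 enrolled).

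**The case against.** The best reply is that one completed cycle is a minimum. Nothing forbids a later look, and the 16% figure suggests that the authors had 25 fully followed patients in mind. Counting immature patients as failures is also a reading, since section 11.4 is silent. Both points stand, and the conclusion is therefore conditional on that reading. They do not rescue the text: no later date is given, and the date that the implied denominator requires is about five months after the earliest one permitted.

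Three stronger readings are tempting, and the documents do not support them.
- A reader might infer that the criterion triggers whatever the drug does. That is exact only under even entry at 4 per month or faster. Section 3.1 gives the rate as approximate. With Poisson accrual the probability falls to 0.85 at a 50% six-month rate, and at 2 per month the result clearly depends on the drug.
- A reader might infer that the trial would be stopped for futility. The stated consequence is suspension pending committee review. Section 11.4 also requires a consensus decision by the consortium, CTEP and the sponsor to stop early, and itself cautions that the endpoint is not a validated surrogate for survival. A committee shown 4 mature patients could see how little they say.
- A reader might infer that the 80% and 90% power statements are wrong because they ignore this rule. They reproduce as fixed 52-event calculations. A suspension that leads to review is not a binding loss of power, so this is no error in section 11.2.

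**Conclusion.** The fault is real and lies in the match of timing, denominator and endpoint within section 11.4. At the planned accrual rate, and with patients short of 26 weeks counted as not having achieved the endpoint, the criterion is met with certainty under even entry. Under Poisson accrual the probability is about 0.997 at a true rate of 15%, 0.98 at 24% and 0.97 at 30%; it is lower if accrual is slower. A trigger that hardly varies between 15% and 30% tells the committee nothing useful about activity. The harm is an uninformative pause at about half accrual or, if the team waits, a look at about month 12.2 with 48 to 49 of 56 patients enrolled and a late toxicity check. The primary survival analysis and the stated power are not affected. The rule should be corrected before it is applied.

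**What to change.** Split the look in section 11.4.

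1. Keep the toxicity criterion at 25 patients with at least one cycle.
2. Apply the progression-free criterion separately to the first 25 patients, using only known 26-week status. Refer the trial to the monitoring committee when the 21st of them has progressed or died before week 26. A patient still progression-free and short of week 26 counts neither way until that date. This keeps the existing cut of 4 in 25.
3. State the rule's suspension probabilities: 0.68 at a true six-month rate of 15%, 0.42 at 20%, 0.24 at 24% and 0.09 at 30%, marking the rates other than 15% as assumptions.

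At a true rate of 15%, when the rule triggers it does so at a median of about month 9 to 10 with about 36 to 40 enrolled, depending on how progression is detected, against month 12.2 and 48 to 49 if all 25 are awaited.

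A smaller change would be to keep a single count but state its date and who is counted. That removes the contradiction but leaves the late timing.

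The cost is a rewording of section 11.4 and a running count of failures among the first 25 patients. No new data are needed.
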